### **7.7. Natriuretic Peptides**

The outcome of the relative change in natriuretic peptide levels at up to 12 months will be analyzed separately for BNP and NT-proBNP. A linear regression model will be used to assess the relative change (i.e., follow-up value divided by baseline value), with adjustments for baseline values. Results will be presented as mean differences in relative change between treatment groups, along with corresponding 95% confidence intervals. If the 12-month assessment is not available, an alternative measurement obtained during the follow-up period will be used. Patients without any measurement of the respective peptide during follow-up will be excluded from this analysis.

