#### **3.2. Secondary Objectives**

The primary secondary objective is to assess the superiority of conduction system pacing over biventricular pacing with respect to total direct medical cost. Additional secondary objectives, evaluated over a 12-month follow-up period, aim to compare both treatment arms regarding: time to first event (composite of all-cause mortality, heart failure hospitalization, or urgent heart failure visits); change in left ventricular ejection fraction (LVEF); change in left ventricular end-diastolic volume; change in Kansas City Cardiomyopathy Questionnaire (KCCQ) Overall Summary Score (OSS); change in New York Heart Association (NYHA) functional class; change in six-minute walk test (6MWT) distance; change in B-type Natriuretic Peptide (BNP) and N-terminal pro-B-type Natriuretic Peptide (NT-proBNP) levels; change in EuroQol-5D (EQ-5D) score; change in QRS duration; and a hierarchical composite endpoint including death, heart failure hospitalization, urgent HF visits, and change in KCCQ Clinical Summary Score (CSS).

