#### 4.4.2. Secondary

#### Outcomes

The main secondary outcome is the total direct medical cost associated with conduction system pacing compared with biventricular pacing. This comparison will be conducted in the modified intention-to-treat (mITT) population, and the time frame for the analysis will correspond to the duration of clinical trial follow-up. The additional secondary outcomes, assessed up to 12 months, include:

1. Time to death, heart failure hospitalization, or urgent visit for heart failure
2. Left ventricular ejection fraction (LVEF)
3. Left ventricular end-diastolic volume
4. Kansas City Cardiomyopathy Questionnaire – Overall Summary Score (KCCQ-OSS)
5. New York Heart Association (NYHA) functional class
6. 6-minute walk test (6MWT)
7. BNP or NT-proBNP levels
8. EuroQol-5D (EQ-5D)
9. QRS complex duration
10. Hierarchical composite outcome including death, heart failure hospitalization, urgent HF visit, and change in KCCQ Clinical Summary Score (CSS)

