#### **4.8. Timing of Outcome Assessments**

Following CRT implantation, all patients will be evaluated in person at a follow-up visit scheduled for 30 days  $\pm$  5 days post-index procedure to assess device parameters and identify potential procedure-related complications. The primary purpose of this visit is to ensure that the patient is in a stable clinical condition and to ensure that no lead dislodgement has occurred.

Subsequent follow-up will take place at 6 months  $\pm$  20 days through a second in-person visit at the enrolling center. During this visit, a comprehensive clinical evaluation will be conducted, including a reassessment of all baseline measures: laboratory tests (including BNP or NT-proBNP), electrocardiogram, echocardiogram, Kansas City Cardiomyopathy Questionnaire (KCCQ), EQ-5D, 6-minute walk test (6MWT), and cardiopulmonary exercise testing (for those enrolled in the sub-study). The follow-up period will be calculated from the date of the index procedure. For example, follow-up day 30 is defined as 30 calendar days after the index cardiac resynchronization therapy procedure (either conduction system or biventricular pacing).

The final visit will occur at 12 months  $\pm$  20 days, during which all previously described assessments will be repeated.

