## APPENDIX A

Four power simulations were conducted using 10,000 iterations each, assuming a total sample size of 180 patients (90 per group) and odds ratio non-inferiority margins of 1.0, 1.1, 1.2, and 1.3.

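### Section 7.7 models BNP and NT-proBNP as untransformed follow-up/baseline ratios, which costs precision and stability if peptides are right-skewed; a log-ratio model is better, and Table 2 should match it

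*Combined protocol and SAP*

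**What the plan says.** Section 7.7 defines the peptide outcome as a relative change and the analysis as follows: "A linear regression model will be used to assess the relative change (i.e., follow-up value divided by baseline value), with adjustments for baseline values". On reporting it says: "Results will be presented as mean differences in relative change between treatment groups". The two peptides "will be analyzed separately for BNP and NT-proBNP", and "Patients without any measurement of the respective peptide during follow-up will be excluded from this analysis". The natural reading is that both the ratio and the baseline covariate enter untransformed.

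No log transform, robust method or alternative scale for the peptides appears in Section 7.7, in Section 7.9 (other secondary outcomes) or in Section 7.10 (sensitivity analyses). Table 2 in Section 7.9 has a row for each peptide, labelled in pg/ml, with a mean difference as the effect measure.

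The documents differ on which peptide is measured. The secondary outcome list in Section 4.4.2 has "BNP or NT-proBNP levels" as a single item, and the visit schedule in Section 4.8 also offers one or the other. The objective in Section 3.2 is worded as "change in B-type Natriuretic Peptide (BNP) and N-terminal pro-B-type Natriuretic Peptide (NT-proBNP) levels", and Section 7.3 lists both at baseline. The number of patients expected to have each assay is not stated.

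**The concern.** A ratio with the baseline value in its denominator is asymmetric: a halving is 0.5 below no change, a doubling 1.0 above it. If peptides are right-skewed, so is the ratio, and its spread grows with its mean. Patients with low baseline values tend to produce the largest ratios. The ratio is also not linear in baseline. If log follow-up is linear in log baseline with slope ρ, the expected ratio is proportional to baseline raised to the power ρ − 1, which is a curve.

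Linear regression of the raw ratio on raw baseline can therefore let a handful of patients decide the estimate and widen its interval. A real proportional difference between arms could be missed, or the reported effect could depend on two or three patients. The SAP takes account of skewness elsewhere: Section 7.5.1 gives costs a gamma model with log link and a bootstrap.

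Table 2 adds a smaller problem. A unit-free difference of ratios (Section 7.7) and a difference in pg/ml (Table 2) are different quantities, and the shell should show the one that the text defines.

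**Working it through.** **The plan's own figure.** The only stated power is for the primary outcome. A simulation of an unadjusted proportional odds model with the Appendix A inputs (180 patients, 5% loss, margin 1.2) gives 81.7%, against 81.4% stated. No power, SD or effect size is given for the peptides.

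**Inputs from the documents.** N = 180, 1:1 allocation, two-sided alpha 0.05, 5% loss, 6.24% mortality. Analysable patients: 180 × 0.95 × (1 − 0.0624) = 160, or 80 per arm. The 40-per-arm case illustrates an even split between assays, which the documents do not state.

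**Assumptions not in the documents.** Baseline and follow-up are log-normal with the same log-SD, 0.6 to 1.2; correlation 0.5 to 0.8; true geometric mean ratio (CSP to BiVP) 0.70.

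**Models compared at equal n**, 4,000 simulated trials per setting:
- planned: follow-up/baseline on arm and baseline
- log scale: log(follow-up/baseline) on arm and log baseline

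Power in %, planned → log scale:

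| log-SD | corr. | 40 per arm | gain | 80 per arm | gain |
|---|---|---|---|---|---|
| 0.6 | 0.5 | 73.5 → 85.0 | 11.5 | 95.6 → 99.1 | 3.5 |
| 0.6 | 0.8 | 98.3 → 99.1 | 0.8 | 100 → 100 | 0 |
| 0.8 | 0.5 | 44.4 → 62.9 | 18.5 | 72.7 → 90.1 | 17.4 |
| 0.8 | 0.7 | 67.9 → 78.5 | 10.6 | 93.2 → 97.9 | 4.7 |
| 0.8 | 0.8 | 85.7 → 90.0 | 4.3 | 99.3 → 99.8 | 0.5 |
| 1.0 | 0.5 | 27.0 → 44.5 | 17.5 | 45.7 → 73.0 | 27.3 |
| 1.0 | 0.7 | 45.6 → 59.6 | 14.0 | 73.2 → 87.8 | 14.6 |
| 1.0 | 0.8 | 64.1 → 73.9 | 9.8 | 90.3 → 95.8 | 5.5 |
| 1.2 | 0.5 | 16.7 → 33.3 | 16.6 | 29.8 → 57.9 | 28.1 |
| 1.2 | 0.7 | 29.8 → 45.7 | 15.9 | 52.0 → 74.6 | 22.6 |
| 1.2 | 0.8 | 46.5 → 57.7 | 11.2 | 73.1 → 87.1 | 14.0 |

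In the six settings where the planned model has under 50% power at 40 per arm, the gain is 11.2 to 18.5 points at 40 per arm and 14.0 to 28.1 at 80 per arm. In the other five it is 0.8 to 11.5 and 0 to 5.5. A separate simulation of the same comparison gave about 15 to 18 and 12 to 28 points in most settings, again with almost none at log-SD 0.6 and correlation 0.8. With a weaker true ratio of 0.80 (log-SD 0.8 to 1.2, correlation 0.5 or 0.7) the gain is about 7 to 10 points at 40 per arm and 11 to 16 at 80 per arm.

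**Closed-form check of the log model.** The residual SD is log-SD × √(1 − ρ²). For log-SD 1.0 and ρ = 0.5 it is 0.866. At 80 per arm the standard error is 0.866 × √(2/80) = 0.137. With ln(1/0.70) = 0.357, power is Φ(0.357/0.137 − 1.96) = 74%, against 73.0% simulated. At 40 per arm it is 45%, against 44.5%.

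**Influence, 80 patients in total.** The three largest ratios carry a median of 40 to 65% of the ratio's sum of squares (log-SD 0.8 to 1.2, correlation 0.5 or 0.7). Dropping those three moves the planned estimate by a median of 0.64 to 0.88 standard errors, against 0.29 to 0.58 on the log scale (log-SD 0.6 to 1.2, correlation 0.5 to 0.8).

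**Validity of the planned model.** Type I error was 3.5 to 5.2%, and coverage of the 95% interval for its own target was 94.4 to 95.5%.

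**The case against.** The strongest defence is that the planned analysis is valid. A reader might infer from the skewness and the curved relation to baseline that the intervals cannot be trusted. The simulations do not support that: with 1:1 allocation and these sample sizes, coverage and type I error are about nominal even in strongly skewed settings. This part of the defence stands in full.

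Second, a reader might compare the planned model in half the sample with a log model that pools both assays, and conclude that most of the power is lost. At log-SD 1.0 and correlation 0.5 that comparison runs from 27% to 72%. It combines a change of scale, worth about 18 points at 40 per arm, with a doubling of n. The doubling presumes an even split with one assay per patient. The wording in Sections 4.4.2 and 4.8 suggests one assay each; Sections 3.2 and 7.3 suggest both; no section gives counts. Analysing the assays separately is also defensible in itself, because a single pooled effect assumes the same proportional effect on two analytes.

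Third, the simulated data are exactly log-normal with a constant multiplicative effect, which favours the log model, and with low variability and high correlation the gain disappears. That limits the size of the claim. It gives no reason to prefer the raw ratio, which did no better than the log scale in power in any setting tried.

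Fourth, the Table 2 units could describe the arm columns only, and Section 7.7 defines the effect. That is a fair reading, so it does not follow that two different effects would be reported. The effect column still needs a label that agrees with the text.

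**Conclusion.** The point holds as one of efficiency and robustness. The raw ratio in linear regression is the weaker choice for a quantity that is likely to be right-skewed, and the plan contains no alternative to it. Under the stated assumptions the log-scale model gains about 11 to 19 power points at 40 per arm and 14 to 28 at 80 per arm in the noisier settings, and little or nothing where variability is low and correlation high. The real gain cannot be fixed from the documents, because they give no peptide SD, correlation, expected effect or assay counts.

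The documents do not support claims that the planned intervals are unreliable, that most of the power is lost, or that each patient has only one peptide. The peptides are one of ten additional secondary outcomes, with no margin or power target, so the primary conclusion, the sample size and the cost endpoint are untouched.

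**What to change.** In Section 7.7, for each peptide, regress log(follow-up/baseline) on treatment and log baseline. Exponentiate the treatment coefficient and its limits, and report the geometric mean ratio with 95% CI. The existing rules on alternative follow-up measurements and exclusions can stay.

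In Table 2, change the effect measure for the BNP and NT-proBNP rows to that ratio, and keep pg/ml only for the descriptive arm summaries.

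Report the number of patients with each assay. Optionally, add a supportive combined model with an assay term, with the separate analyses remaining the main ones.

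The cost is SAP wording and one table shell, with no new data. The downside is interpretive: the effect is read as a ratio of geometric means and no longer as an arithmetic mean difference.

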### **7.8. Functional Class**

NYHA functional class at 12 months will be described using absolute and relative frequencies and compared between treatment groups using ordinal regression models similar to the one used for the primary outcome, adjusted for baseline NYHA class. Results will be reported as proportional odds ratios, consistent with the primary outcome analysis.

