### 4.4. **Outcome Definitions and Measurements**

#### 4.4.1. *Primary Outcome*

The primary outcome, defined as “*heart failure–related net clinical outcome*,” will be assessed as an ordinal hierarchical composite outcome compared between groups using a proportional odds model. The ordinal scale will consist of the following (in hierarchical order):

1. All-cause mortality
2. Heart failure hospitalization
3. Urgent visit due to heart failure
4. Absolute change in left ventricular ejection fraction (LVEF) from baseline to 12-month follow-up, categorized into 5% intervals (e.g.,  $(-10, -5]$ ,  $(-5, 0]$ ,  $(0, +5]$ ,  $(+5, +10]$ ).

All-cause mortality was assigned the top-weighted category in the ordinal scale, and the greatest improvement in LVEF was assigned the lowest-weighted category. The study will assess whether conduction system pacing (CSP) is non-inferior to biventricular pacing (BiVP).

The non-inferiority margin will be defined as an upper bound of the 95% confidence interval (CI) for an odds ratio  $<1.2$ . If CSP reaches the non-inferiority bound, superiority will then be tested using the same proportional odds model with alpha preservation.

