### **7.9. Other Secondary Outcomes**

Secondary outcomes assessed up to 12 months will be analyzed using linear regression models adjusted for baseline values. Treatment effects will be reported as mean differences with corresponding 95% confidence intervals. If a patient does not have a 12-month outcome assessment, an alternative measurement obtained during the study follow-up will be used. Patients with no measurements for a given variable during follow-up will be excluded from that specific analysis. **Table 2** provides a proposed summary of the secondary outcome effects.

**Table 2.** Comparative Analysis of Secondary Outcomes by Treatment Group

| Secondary Outcomes                                  | Biventricular Pacing
[control] | Conduction System
Pacing
[intervention] | Effect
Measure | Effect
[95% CI] | p-value |
|-----------------------------------------------------|-----------------------------------|-----------------------------------------------|-------------------|--------------------|---------|
| Echocardiographic Outcomes                   |                                   |                                               |                   |                    |         |
| Ejection fraction (%)                               | xx.x (xx.x)                       | xx.x (xx.x)                                   | Mean dif.         | x.xx [x.xx - x.xx] | x.xxx   |
| End-diastolic volume (ml)                           | xx.x (xx.x)                       | xx.x (xx.x)                                   | Mean dif.         | x.xx [x.xx - x.xx] | x.xxx   |
| Electrocardiographic and laboratory outcomes |                                   |                                               |                   |                    |         |
| Change in QRS duration (ms)                         | xx.x (xx.x)                       | xx.x (xx.x)                                   | Mean dif.         | x.xx [x.xx - x.xx] | x.xxx   |
| BNP (pg/ml)                                         | xx.x (xx.x)                       | xx.x (xx.x)                                   | Mean dif.         | x.xx [x.xx - x.xx] | x.xxx   |
| NT-proBNP (pg/ml)                                   | xx.x (xx.x)                       | xx.x (xx.x)                                   | Mean dif.         | x.xx [x.xx - x.xx] | x.xxx   |

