### 7.12. Functional Capacity Sub-study

#### *Cardiopulmonary Exercise Testing*

Cardiopulmonary exercise test (CPET) outcomes up to 12 months will be analyzed using linear regression models adjusted for baseline values. Effects will be reported as mean differences between treatment groups with corresponding 95% confidence intervals.

If the CPET is not performed at the 12-month visit, an alternative assessment obtained during the follow-up period will be used. If no follow-up measurement of the variable is available, the patient will be excluded from the corresponding analysis.

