### **7.13. Missing Data**

Imputation strategies for the primary and secondary efficacy endpoints are defined within their respective analysis sections. For other exploratory outcomes, minimal missing data are anticipated given the study's structured procedures, which include site staff training and independent data monitoring.

Nevertheless, the coordinating center will contact the site investigators to obtain any missing data variables. Analyses for primary and secondary outcomes will be performed based on participants with available outcome data (i.e., available case analysis), except for the specific imputation approaches already outlined for the primary endpoint, the economic secondary endpoint, and the ordinal secondary endpoint as detailed in the Outcomes Analysis section.

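### The NYHA analysis in 7.8 has no level for patients who die before 12 months, so unequal deaths could make the arm with more deaths look functionally better (minor, secondary outcome)

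*Combined protocol and SAP*

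**What the plan says.** NYHA class is one of the additional secondary outcomes in 4.4.2. Section 7.8 describes it at 12 months, "compared between treatment groups using ordinal regression models similar to the one used for the primary outcome, adjusted for baseline NYHA class", with results reported as proportional odds ratios. It gives no rule for death or for a missing class. Table 2 has rows for classes I to IV and shows a separate mean difference for each.

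The general rule is in 7.13: "Analyses for primary and secondary outcomes will be performed based on participants with available outcome data (i.e., available case analysis". The exceptions are the primary, economic and ordinal secondary endpoints, and NYHA is not among them.

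For the outcomes under 7.9 the rule is explicit. "If a patient does not have a 12-month outcome assessment, an alternative measurement obtained during the study follow-up will be used", and "Patients with no measurements for a given variable during follow-up will be excluded from that specific analysis". Sections 7.7 and 7.12 do the same for natriuretic peptides and exercise testing. None of these separates death from a missed visit. The earlier value would normally come from the second in-person visit in 4.8 ("Subsequent follow-up will take place at 6 months"). Section 7.14 has a rule for heart transplantation in non-clinical endpoints but none for death.

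The primary scale treats death differently: "All-cause mortality was assigned the top-weighted category in the ordinal scale". The hierarchical KCCQ-CSS outcome in 7.6 also includes death.

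**The concern.** A patient who dies before 12 months has no NYHA class. If such patients leave the analysis, the comparison is between survivors and no longer between the groups as randomized. Deaths in heart failure tend to come from the worse classes, so an arm that loses more patients loses them from the bad end of its distribution, and its remaining patients look better. In a non-inferiority trial the functional outcomes will be read as supporting evidence, and a result that improves because patients died would mislead.

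NYHA is also where a remedy is simplest. The outcome is already ordinal, the model is described as similar to the primary one, and the primary scale already ranks death worst. LVEF and KCCQ-CSS have a counterpart that includes death in the two hierarchical outcomes. NYHA has none.

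**Working it through.** **Expected deaths.** The plan gives no figure for NYHA, so its mortality assumption is the starting point. Section 4.5 extrapolates 20.8% over 40 months linearly: 20.8% × 12/40 = 6.24%, as in Appendix A. With 90 per arm this gives 90 × 0.0624 = 5.6 deaths per arm and 180 × 0.0624 = 11.2 in total.

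**Chance imbalance.** With two independent binomials (90, 0.0624), the probability that the arms differ by 3 or more deaths is 44%. The probability that one arm has at least twice the deaths of the other is 32%. Equal true risk therefore does not guarantee similar observed deaths.

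**Check of the fitting method.** An unadjusted proportional odds fit to simulated primary outcomes (Appendix A parameters, 85 evaluable per arm) gave 81.4% power at the 1.2 margin. Appendix A states 81.4%.

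**Illustration A.** These inputs are assumptions, not document figures:
- NYHA I/II/III/IV is 25/50/20/5% in both arms if nobody died, so there is no true functional difference.
- 70% of deaths come from class III and 30% from class IV.
- There are 85.5 patients per arm (90 × 0.95).
- Mortality is 6.24% versus 12.48%.

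Expected counts:

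| Level | 6.24% arm | 12.48% arm |
|---|---|---|
| I | 21.38 | 21.38 |
| II | 42.75 | 42.75 |
| III | 85.5 × (0.20 − 0.7 × 0.0624) = 13.37 | 85.5 × (0.20 − 0.7 × 0.1248) = 9.63 |
| IV | 85.5 × (0.05 − 0.3 × 0.0624) = 2.67 | 85.5 × (0.05 − 0.3 × 0.1248) = 1.07 |
| Dead | 5.34 | 10.67 |

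Among survivors, class III–IV makes up 16.04/80.16 = 20.0% in one arm and 10.70/74.83 = 14.3% in the arm with more deaths. The odds ratio for a worse class is 53.45/58.79 = 0.91 at the I/II cut and 10.70/16.04 = 0.67 at the II/III cut. The fitted common odds ratio is 0.80.

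Results for the arm with more deaths (above 1 means worse). The carried column assumes that half the deaths fall after month 6 and that their 6-month classes were 30% II, 60% III and 10% IV.

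| Mortality | Deaths excluded | 6-month class carried | Death ranked worst |
|---|---|---|---|
| 6.24% vs 6.24% | 1.00 | 1.00 | 1.00 |
| 6.24% vs 9.36% | 0.90 | 0.94 | 1.02 |
| 6.24% vs 12.48% | 0.80 | 0.88 | 1.05 |
| 3% vs 12.48% | 0.73 | 0.82 | 1.08 |

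At doubled mortality, two other assumed mixes (40/40/16/4% and 15/45/33/7%) gave 0.80 and 0.84 with deaths excluded, and 1.04 and 1.08 with death ranked worst.

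**Illustration B.** Assumed mix 30/50/18/2%, with a latent severity driving both class and death, and 86 versus 85 patients. Mortality of 12.5% versus 6.2% gave 0.88 excluded, 0.93 carried and 1.13 with death worst. Mortality of 9% versus 3.5% gave 0.88 excluded and 1.08 with death worst. Equal mortality gave about 1.0 either way.

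**If deaths are unrelated to class.** Exclusion gives 1.00 in every case. Death ranked worst gives 1.11 to 1.38 across the unequal-mortality cases.

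**Size against precision.** In illustration A the standard error of the log odds ratio with deaths excluded is 0.31. At 0.80, exp(−0.219 ± 1.96 × 0.31) runs from 0.44 to 1.48, so the shift is 0.219/0.31 = 0.7 standard errors. An odds ratio of 0.88 is about 0.4 standard errors from 1.

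All the NYHA fits omit the baseline-class adjustment in 7.8, which would absorb whatever part of the severity it captures.

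**The case against.** Several counter-arguments are sound. Section 7.8 is silent, so leaving out deaths is inferred from 7.13. NYHA sits in the table attached to 7.9, and if that fallback applies the bias is smaller. Table 2 is only a proposed layout and does not prove a four-level model. Under the plan's own equal mortality there is no expected bias, and otherwise the shift is well inside the confidence interval.

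The strongest objection concerns the estimand. With death ranked worst, an odds ratio above 1 can arise from mortality alone, under a functional label. That stands, and it is why the survivors-only result should be kept beside it. It does not justify leaving the rule unstated.

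A reader might infer that excess deaths would go unseen. The documents do not support that: death ranks worst in the primary outcome, counts in the time-to-event composite, and has its own line by arm with a hazard ratio in Table 1.

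A reader might also want 7.9 to substitute earlier values only for patients alive at 12 months. That would remove late deaths, whom 7.9 now keeps. In two checks on a continuous outcome with about double the mortality and severity-related deaths, the spurious difference rose from about 0.03–0.04 SD under the present rule to 0.06–0.07 SD among survivors only.

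**Conclusion.** The point holds as a minor one on a secondary outcome. As written, the NYHA odds ratio most likely compares survivors, or counts late deaths at their 6-month class. It can favour the arm with more deaths when two conditions hold together: mortality differs by effect or by chance, and deaths come from sicker patients. At about double the mortality the spurious odds ratio is roughly 0.80 to 0.88 with deaths excluded, or 0.88 to 0.93 with the 6-month class carried. These figures rest on assumed NYHA mixes and death rates.

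The documents do not support predicting which arm would benefit, since they assume equal mortality. Nor do they support extending the point to the primary non-inferiority test or the sample size, where death is already ranked.

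The Table 2 mismatch is separate and needs no assumption: 7.8 specifies a proportional odds ratio and the table shows four mean differences.

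**What to change.** 1. In 7.8, analyse five ordered levels at 12 months (I, II, III, IV, dead) with the proportional odds model already stated, adjusted for baseline class.
2. Report the survivors-only odds ratio as a supportive result, and say that the main odds ratio combines function and death.
3. In Table 2, replace the four NYHA mean-difference cells with the single odds ratio that 7.8 specifies, and add a row for deaths.
4. Leave the substitution rule in 7.9 as it is.

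The cost is a few lines of SAP wording and one table row. No new data are needed, because all deaths are already collected and adjudicated. The price is a less pure functional measure, which the supportive result offsets. The death level repairs NYHA only. The outcomes analysed by linear regression keep their present handling.
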